# Efficacy of Bushen Huatan Decoction combined with Baduanjin in the treatment of polycystic ovary syndrome with insulin resistance (IR-PCOS), kidney deficiency and phlegm dampness: study protocol for a randomized controlled trial

**DOI:** 10.1186/s13063-021-05770-z

**Published:** 2021-11-07

**Keywords:** Polycystic ovary syndrome, Insulin resistance, Bushen Huatan Decoction, Baduanjin

## Abstract

**Background:**

Polycystic ovary syndrome (PCOS) is a common reproductive endocrine disease in women. Insulin resistance (IR) has emerged as a central contributor to the pathogenesis of this disease. According to traditional Chinese medicine (TCM), kidney deficiency is the main syndrome of PCOS. The deficiency of the kidney cannot vaporize water-dampness, and the retention of water-dampness accumulates into phlegm dampness stagnation, resulting in visceral dysfunction and metabolic disorder. TCM involving syndrome differentiation and treatment is widely used to adjust women’s menstrual cycles. Our patented formula Bushen Huatan Decoction (BSHTD) has been proven to be effective in the clinical treatment of IR-PCOS. Baduanjin also plays an important role in improving metabolic syndrome through lifestyle intervention. This study investigates the clinical efficacy of Bushen Huatan Decoction combined with Baduanjin in IR-PCOS, to form a specific TCM-behaviour intervention plan in the treatment of IR-PCOS.

**Methods/design:**

This is a randomized controlled trial involving 190 participants diagnosed with IR-PCOS. All participants will be randomly allocated into 5 groups: group A will receive metformin; group B, BSHTD; group C, Baduanjin; group D, BSHTD combined with metformin; and group E, BSHTD combined with Baduanjin. One course of treatment lasts 3 months, a total of two courses. The primary outcomes are changes in the homeostatic model assessment of insulin resistance (HOMA-IR) and improvements in the oral glucose tolerance test (OGTT) and insulin-releasing test (INS). The secondary outcomes are improvements in the menstrual cycle, ovulation rate, clinical pregnancy rate, basic serum sex hormone levels, free androgen index (FAI), Ferriman-Gallwey scores, body mass index (BMI) and TCM syndrome scores. The related observation indexes will be collected at baseline, during the process of treatment and at the 6-month follow-up. Simultaneously, close monitoring of possible adverse events will be performed throughout the trial process.

**Discussion:**

This trial will investigate the efficacy of the comprehensive intervention program of Bushen Huatan Decoction combined with Baduanjin on the adjustment of the menstrual cycle, improvement of insulin resistance and correction of glucose metabolism disorder in IR-PCOS patients. It is expected to form an alternative treatment of TCM-behaviour intervention therapy for IR-PCOS and promote the Chinese fitness Qigong Baduanjin in the application of lifestyle diseases.

**Trial registration:**

Chinese Clinical Trial Registry ChiCTR2100043415. Registered on 15 February 2021.

**Supplementary Information:**

The online version contains supplementary material available at 10.1186/s13063-021-05770-z.

## Background

Polycystic ovary syndrome (PCOS) is one of the most common reproductive endocrine and metabolic disorders in modern women and affects approximately 4% to 8% of women of childbearing age worldwide [1]. With the acceleration of life rhythm and transformation of lifestyle, the incidence of this disease is increasing year by year and has become one of the main causes of female ovulation disorder infertility [2]. The clinical manifestations of PCOS are highly heterogeneous and complex; doctor’s office visits usually occur for patients’ oligomenorrhoea, amenorrhoea, infertility, abnormal uterine bleeding, obesity, hirsutism, acne, etc.

At present, the pathogenesis of PCOS is not completely clear; there is growing evidence that PCOS may be a complex polygenic disease and under the influence of epigenetics and the environment, accompanied by a chronic low-grade pro-inflammatory state [3]. Insulin resistance (IR) is the central link in the occurrence of this disease [4], and the mechanism is related to abnormalities in the insulin receptor signal transduction pathway [5]. Obesity-induced IR and hyperandrogenemia are independent factors for the evolution of PCOS. If the patients’ metabolic imbalance and endocrine disorders are not corrected in a reasonable length of time, long term complications associated with PCOS including abnormal metabolism of glucose and lipids, cardiovascular and cerebrovascular diseases, oestrogen-dependent tumours (such as breast cancer and endometrial cancer) and mental illness can seriously affect a woman’s quality of life and threaten her health [6].

According to TCM, the pathogenesis of PCOS is based on deficiency of spleen and kidney, with phlegm dampness and blood stasis as the appearance, especially kidney deficiency and phlegm dampness as the most common pathological type of PCOS. Kidney deficiency includes insufficiency of kidney-essence, kidney-Qi, kidney-Yin, kidney-Yang and other aspects, which can lead to insufficiency of generating essence and transforming blood, thus affecting the cycle of menstruation and embryo breeding. Patients with IR-PCOS tend to have a fat-greasy diet, coupled with a lack of good lifestyle and exercise, resulting in phlegm dampness congestion and hindrance of functional activities of Qi, so that disharmony of Chong and Ren channels and amenorrhoea. In addition, clinical symptoms such as follicular growth restriction, ovulation dysfunction and abnormal metabolism of glucose and lipid caused by kidney deficiency and phlegm dampness are closely related to the pathological link of insulin resistance.

The main treatment strategies for PCOS are correcting insulin resistance, improving hyperandrogenemia and its signs, and promoting ovulation and fertility [7]. A growing number of studies and guidelines recommend lifestyle adjustment as the first-line treatment for PCOS. Lifestyle intervention is mainly reflected by alterations in diet, exercise, sleep, emotion and so on. As a kind of gradual approach, exercise intervention should be carried out scientifically and rationally. Baduanjin is a form of traditional Chinese exercise Qigong that follows the theoretical system of TCM. Its movements consist of eight separate parts, and it leads to adjustments to overall physical fitness through the movement of the muscles and joints, the control of breathing, and the concentration of the mind [8], so as to maintain the harmony between Qi and blood, keep Yin and Yang in balance. It plays an active role in the treatment of chronic diseases and metabolic syndrome [9]. Traditional Chinese medicine has been widely used in the treatment of metabolic syndrome; our previous basic study confirmed that Bushen Huatan Decoction can activate the PI3K/AKT pathway [10] and increase the expression levels of insulin receptor (INSR) and IRS-1 protein in adipose tissue of IR-PCOS model rats, thus improving glucose and lipid metabolism and insulin resistance in rats. In addition, our clinical process has proven that Bushen Huatan Decoction can obviously improve insulin sensitivity, reduce androgen levels and correct reproductive cycles.

Therefore, we will combine Bushen Huatan Decoction with Baduanjin to intervene in IR-PCOS of kidney deficiency and phlegm dampness in this trial, evaluate its clinical efficacy and examine the advantages of traditional Chinese medicine and Chinese Qigong exercise in the treatment of this disease to form a specific combined program of TCM-behaviour intervention for IR-PCOS of kidney deficiency and phlegm dampness, to maintain patients’ health and improve their quality of life.

## Methods/design

### Study design

This is a factorial-design randomized controlled clinical trial. Multi-channel intervention of IR-PCOS will be evaluated simultaneously by treating the different combinations of metformin, BSHTD and Baduanjin exercise, so as to find the best intervention scheme for the treatment of this disease. The research protocol is compliant with the Consolidated Standards of Reporting Trials (CONSORT) guidelines [11] as well as the Standard Protocol Items: Recommendations for Interventional Trials (SPIRIT) statement [12]. The SPIRIT checklist is presented in additional file 1.

This study has been approved by the ethics committee of Zhangjiagang TCM Hospital Affiliated to Nanjing University of Chinese Medicine. The patients will be recruited from the Department of Reproduction of Zhangjiagang TCM Hospital Affiliated to Nanjing University of Chinese Medicine. Informed consent will be obtained from each participant before the study procedure is performed according to good clinical practice. This trial has been registered at the Chinese Clinical Trial Registry (ChiCTR2100043415) and conducted in accordance with the Declaration of Helsinki.

### Participants

A total of 190 patients who met the inclusion criteria without any exclusion criteria will be recruited in this study through the physicians from the department of reproduction of Zhangjiagang TCM Hospital Affiliated to Nanjing University of Chinese Medicine. All participants will be provided with the background information, purpose, possible benefits and harms of this study before signing informed consent. The written documents related to informed consent will be signed face-to-face by physicians and patients during outpatient diagnosis and treatment and will be kept by a member of the project team who will never be involved in the clinical data collection throughout the whole process. The recruitment plan will begin in March 2021 and be completed in March 2022.

#### Inclusion criteria

Chinese women aged from 18 to 35 years old.BMI [13] over 25.0 kg/m^2^.Confirmed diagnosis of PCOS according to the 2003 Rotterdam criteria [14]: (a) irregular menstruation cycles (a periodic interval > 35 days or < 8 cycles in a year) or amenorrhoea (a periodic interval > 90 days) or abnormal uterine bleeding; (b) clinical manifestations of hyperandrogenism (hirsutism in mainland China is taken as Ferriman-Gallwey score ≥5 [15]) and/or hyperandrogenemia [free androgen index (FAI)=total testosterone (nmol/L)/SHBG (nmol/L)×100 > 4.5 [16]]; and (c) transvaginal ultrasonography showing PCOM: the number of follicles with a diameter of 2–9 mm in one or both ovaries ≥12, and/or ovarian volume ≥10 ml [ovarian volume calculation: 0.5 × long diameter (cm) × diameter (cm) × anteroposterior diameter (cm)]. Among all the above, (a) is a necessary condition, and matching one of (b) or (c) represents suspected PCOS, which then requires ruling out other factors and diseases that may cause hyperandrogenism and ovulation dysfunction.In line with the diagnosis criteria of TCM syndrome differentiation: kidney deficiency and phlegm dampness.Confirming the diagnosis of insulin resistance: the criteria of IR are defined according to the homeostatic model assessment of insulin resistance (HOMA-IR) [fasting plasma glucose (mmol/l) × fasting serum insulin (uIU/ml)/22.5]. A value ≥2.29 [17] is considered to be indicative of IR.No history of using hormone drugs or drugs that affect glucose metabolism within the 3 months prior to treatment.Volunteer to participate in this trial and give informed consent.

#### Exclusion criteria

Patients with any other endocrine diseases related to this disease (such as Cushing’s syndrome, congenital adrenal hyperplasia, 21-hydroxylase deficiency, hyperprolactinemia, uncorrected thyroid disease, type 1 or type 2 diabetes mellitus, etc. ).Patients with congenital malformations or defects of the reproductive system, organic lesions of the reproductive system (such as uterine fibroids and ovarian cysts).Patients with reproductive malignancies (such as endometrial cancer and cervical cancer).Patients with genital inflammation, genital tuberculosis, and pelvic inflammatory disease.One of the spouses has a sexually transmitted disease such as syphilis and AIDS.Patients with serious primary diseases of the cardiovascular, cerebrovascular, liver, kidney and hematopoietic systems or psychoses.Patients with chromosomal abnormalities, pregnancy or lactation.Interventions of any other medication treatments, including hormone drugs, drugs that will affect glucose metabolism, Chinese herbal prescriptions or acupuncture in the previous 3 months.Patients allergic to the drugs used in this study.Patients in other clinical trials at the same time.

### Interventions

After baseline measurements, participants satisfying the inclusion criteria will be randomly divided into one of the following 5 clinical groups:
Group A: metformin at a dose of 500 mg per meal, 3 times per day, orally for 2 courses.Group B: BSHTD at a total dose of 400 ml per day, divided into 2 oral, doses for a total of 2 courses.Group C: Baduanjin exercise for 30 min per day, for a total of 2 courses.Group D: BSHTD combined with metformin, orally for 2 courses.Group E: BSHTD combined with Baduanjin exercise, for a total of 2 courses.

#### Group A: Metformin

For the purpose of reducing symptoms of gastrointestinal discomfort caused by metformin, the daily oral dose will be gradually increased from 500 mg during the first week, to 1000 mg during the second week, and to 1500 mg during the third week. From the fourth week onwards, the daily oral dose will be maintained at 500 mg per meal, 3 times per day (orally along with breakfast, lunch and dinner). One course of treatment is three months long, and patients will be given a total of two courses.

#### Group B: Bushen Huatan Decoction

The Bushen Huatan Decoction is composed of 12 g of *Cuscuta chinensis Lam*, 12 g of *Astragali Radix*, 10 g of *Atractylodis Rhizoma*, 12 g of *Cyperi Rhizoma*, 10 g of *Poria*, 9 g of *Pinelliae Rhizoma*, and 6 g of *Citri Reticulatae Pericarpium*. The patients will take a total dose of 400 ml, divided into 2 oral doses per day (1 h after breakfast and 1 h after dinner), and will stop taking it during menstruation. In the course of the trial, the TCM doctor will add or subtract the herbal medicine according to the patients’ systemic and local concomitant symptoms. One course of treatment is three months long, and patients will be given a total of two courses. If a pregnancy test is positive during the course, the Bushen Huatan Decoction will be changed to kidney-nourishing and foetal soothing prescriptions to prevent miscarriage.

#### Group C: Baduanjin exercise

The Baduanjin exercise newly promulgated by the Ministry of Sport of China in 2003 will be adopted in this trial. We will guide the patients to learn Baduanjin exercise through 8 courses and ensure that all participants can master standard movements. After that, the patients will consciously perform these exercises at home once a day, for 30 min each session, and will stop during menstruation. One course of treatment is three months long, and patients will be given a total of two courses. We will provide free training videos and daily training registration cards to urge and monitor practice attendance.

#### Group D: Bushen Huatan Decoction combined with metformin

The patients will take a total dose of 400 ml of Bushen Huatan Decoction, divided into 2 oral doses per day (1 h after breakfast and 1 h after lunch), and stop the intervention during menstruation, together with the daily dose of metformin (the regimen is the same as that of group A).

#### Group E: Bushen Huatan decoction combined with Baduanjin exercise

The daily oral solution of Bushen Huatan Decoction is similar to that of group B; in addition, the participants in this group are required to practice Baduanjin exercise during the stage of the trial (the specific exercise program is similar to that of group C). All interventions will be stopped during menstruation. One course of treatment is three months long, and patients will be given a total of two courses.

#### Follow-up

To assess the accuracy of diagnosis, effectiveness and safety of treatment in individual interventions, a follow-up via face-to-face interview, telephone, WeChat, text message, or e-mail will be conducted 6 months after the final treatment. During this stage, none of the subjects will receive any other therapy other than routine cervical care. The case observers will investigate the situation of all participants, mainly including menstrual cycle, TCM syndromes and signs, the appearance of hyperandrogenism (body weight, excessive hairiness, acne, acanthosis nigricans) and pregnancy. Participants are welcome to inform the assessors of their clinical symptoms at additional times throughout the experimental period.

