### Study-specific visits and procedures

All participants will receive 2 courses of treatment lasting for 6 months and will be followed up for 6 months. All participants will attend a total of 6 visits: screening visit, baseline visit, first course visit, end-of-treatment visit, and two follow-up visits. Simultaneously, close monitoring of possible adverse events during the trial process will be performed. A flowchart of this trial is depicted in Fig. 1. The schedule of trial enrolment, intervention and assessment is expounded in Table 1.

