### Blinding

This study is a single-blinded trial. Outcome assessors and people responsible for statistical analysis will be blinded to the randomization status.

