### Statistical analysis

Clinical data of all participants will be disposed in the final statistical analysis based on the intent-to-treat principle to determine the robustness of the evidence. The data processors will be unaware of the specific allocation situation. Basic indicators will be analysed to test the balance of each group at baseline. Comparisons will be processed based on changes from baseline to the end of the intervention and follow-up. The one-sample Kolmogorov-Smirnov test and graphical methods will be applied to test the normal distribution of continuous variables (such as the levels of basic serum sex hormones, HOMA-IR, ovulation rate, clinical pregnancy rate, BMI, FAI, Ferriman-Gallwey scores and TCM syndrome scores), which will be presented as the mean ± standard deviation if normally distributed and as the median with an interquartile range if not normally distributed. A paired *T* test or the Wilcoxon rank test will be used to compare variables within a group from baseline to the end of the intervention. Analysis of variance (ANOVA) with Bonferroni correction will be carried out to compare differences among groups of continuous variables consistent with a normal distribution. Continuous variables that do not meet the normal distribution will be processed by using the Kruskal-Wallis test followed by the Mann-Whitney *U* test. Categorical variables will be analysed by chi-square statistics when appropriate, and Fisher’s exact test will be used to compare discrete variables with fewer than 5 observations. All data analyses will be processed by the Statistical Package for Social Sciences (SPSS) version 25.0. A *P* value < 0.05 with a two-tailed test and mean difference with 95% confidence intervals will be considered statistically significant.

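### The 6-month follow-up may be done remotely or face-to-face with no mode tied to any outcome, so examined signs and unblinded self-reports can be mixed in the change from baseline to follow-up

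*Protocol article*

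**What the plan says.** Five places in the protocol article bear on this.

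- **Follow-up, mode and purpose.** The aim is given as "To assess the accuracy of diagnosis, effectiveness and safety of treatment in individual interventions". The contact is described as "a follow-up via face-to-face interview, telephone, WeChat, text message, or e-mail will be conducted 6 months after the final treatment".
- **Follow-up, content and collector.** On who collects the data, the section says: "The case observers will investigate the situation of all participants". The content of that enquiry is then given as "mainly including menstrual cycle, TCM syndromes and signs, the appearance of hyperandrogenism (body weight, excessive hairiness, acne, acanthosis nigricans) and pregnancy". No laboratory test is named, but the list is introduced as the main content, not the whole of it.
- **Statistical analysis.** "Comparisons will be processed based on changes from baseline to the end of the intervention and follow-up". The sentence is not restricted to particular outcomes.
- **Abstract, Methods/design.** "The related observation indexes will be collected at baseline, during the process of treatment and at the 6-month follow-up". Again no outcome is singled out.
- **Study-specific visits and procedures.** Participants are to attend six visits: "screening visit, baseline visit, first course visit, end-of-treatment visit, and two follow-up visits".

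The Blinding section adds: "Outcome assessors and people responsible for statistical analysis will be blinded to the randomization status". Participants are not listed as blinded.

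**The concern.** Several of the follow-up items have to be measured or examined. A text message or e-mail can supply only the woman's own account of her weight, hair growth or skin, or at best a picture. She knows whether she was given metformin, decoction or exercise. If one woman is examined and the next is asked by message, the follow-up value does not mean the same thing for both, and the change score carries that difference.

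At stake are the follow-up claims on weight, signs of hyperandrogenism and TCM signs. It is also unclear which outcomes have a follow-up value at all, including the insulin-resistance measures.

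**Working it through.** The plan gives no figure on this point, so the check compares the sections.

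**1. What each outcome needs.**
- *A blood sample:* HOMA-IR, OGTT, INS, sex hormones, FAI. No remote contact can give these.
- *Measurement or examination:* weight/BMI, Ferriman-Gallwey score, acne, acanthosis nigricans, TCM signs. A remote contact gives a report in place of the measurement.
- *The woman's report:* menstrual cycle and pregnancy status. These can be collected remotely, and menstrual history is self-reported in any mode.

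The mode rule therefore fails for the second group, which the Follow-up section itself lists. It does no harm for the third. For the first, the question is whether a follow-up value is intended.

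**2. Is a laboratory follow-up value intended?** The Follow-up section names no blood test. The Abstract and the Statistical analysis section speak of follow-up without restriction, and the latter names HOMA-IR, sex hormones and FAI among its variables, though in its sentence on normality testing. The within-group tests run only to the end of the intervention. The sections do not settle the question. Table 1, the assessment schedule, was not available in the text reviewed.

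**3. Number and kind of contacts.** The Follow-up section describes one contact, possibly remote. Study-specific visits and procedures describes two follow-up visits that are attended. These do not agree.

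**4. Blinding.** Assessors and analysts are blinded. The Follow-up section does not say whether the case observers are those assessors. Even if they are, a sign reported by telephone originates with an unblinded person.

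**5. Comparability with baseline.** Eligibility requires BMI, a Ferriman-Gallwey score and/or FAI where hyperandrogenism is the qualifying feature, and a TCM diagnosis, and consent is taken at outpatient visits. It is a reasonable inference that baseline values come from clinic assessment. A remote follow-up value would then be set against an examined baseline.

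**6. Size of any bias.** Let p1 and p2 be the shares of two arms followed remotely, and d1 and d2 the mean differences between report and examination. The contrast in change scores shifts by p1 × d1 − p2 × d2. If p1 = p2 and d1 = d2, the shift is zero. The documents give neither the shares nor the differences, so no value can be calculated.

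**The case against.** The strongest defence is that attended follow-up is already planned. Participants are to attend two follow-up visits, registration fees during follow-up are funded, and face-to-face is the first mode listed. Remote contact may be only a fallback against loss to follow-up, and the single contact described may be just the last of the two. Table 1 could show what is measured when, and a condensed article may leave detail to the full protocol. This explains how the wording may have arisen. It does not remove it: as written, any woman's effectiveness follow-up may be remote, for any item.

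Three stronger readings are tempting, and the documents do not support them.

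- *That laboratory outcomes are planned at follow-up and will be lost.* Only general wording suggests this. The sample size is set on HOMA-IR after two courses of treatment, and the hypotheses in the Discussion state no HOMA-IR effect at 6 months after treatment. What stands is that the sections leave it unclear.
- *That self-report replaces blinded assessment.* Face-to-face remains possible, and an assessor who telephones can stay blinded. What stands is that remotely reported signs come from an unblinded source.
- *That the false-positive rate is materially inflated.* Suppose half of one arm and none of the other reports remotely, with a bias of 0.5 SD. The shift is 0.25 SD, and 0.25/√(2/30) = 0.97 standard errors with 30 women per arm, which gives about 16% rejections at a nominal 5%. All these inputs are assumed, and nothing in the documents links contact mode to arm. The figure also ignores the planned Bonferroni correction: with ten pairwise contrasts (0.05/10 = 0.005), the same shift gives about 3.3% per contrast. It should not be used as an estimate.

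**Conclusion.** The point holds for the examined and measured follow-up outcomes. The protocol permits two measurement methods for the same outcome without a rule, one of them resting on participants who know their treatment, and this conflicts with the attended follow-up visits stated elsewhere. It also leaves open which outcomes have a follow-up value.

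The size cannot be given. Bias in a between-arm contrast requires contact mode or reporting to differ between arms; the openly different treatments make that possible, but no document shows that it will happen. The conclusion rests on two things: the plain wording of the Follow-up section, and the inference that baseline signs are assessed in clinic. The end-of-treatment HOMA-IR comparison, on which the trial is sized, is not affected. The matter is worth correcting because follow-up effectiveness claims would otherwise be hard to interpret and the correction is cheap.

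**What to change.** Reconcile the Abstract, Follow-up, Study-specific visits and procedures, and Statistical analysis sections.

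- State which outcomes have a follow-up value and at which of the two follow-up visits.
- Take weight/BMI, Ferriman-Gallwey score and TCM sign scores at the attended follow-up visit with the blinded assessor.
- Use remote contact for menstrual dates, pregnancy and adverse events.
- Record the contact mode for every woman. Treat remote-only reports of examined outcomes as missing in the main follow-up comparison, and use them only in a sensitivity analysis.
- If no follow-up blood is drawn, limit the follow-up comparison to non-laboratory outcomes and the insulin-resistance conclusion to the end of treatment.

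The cost is small, since attended follow-up visits are already planned and their registration fees are covered (Patient and public involvement section). The downside is some more missing examined values, from women who will answer a message but not attend.
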